### 491 7.3. Allocation factors

492 (1) Age: 2 levels: 20-64 years old and 65-80 years old

493 (2) OAB severity: 2 levels: OABSS 6-11 points, OABSS 12-15 points

494 (3) Oral treatment: 3 levels: no prior treatment, prior treatment but more than 6 weeks  
495 have passed since the last dose, and currently on oral treatment.

496 (4) Institution: 4 levels (4 facilities)

497 (5) Intervention method: 2 levels: face-to-face, web conference

498 Age is considered the most significant risk factor for OAB, and the understanding of  
499 CBT may differ according to age, and the effectiveness of the intervention may also  
500 differ. We believe that OAB severity strongly influences intervention effectiveness.

501 Intervention effectiveness may differ depending on whether CBT alone or in  
502 combination with oral medication is used. The backgrounds of the participants are  
503 expected to differ between facilities. For these reasons, age, OAB severity, presence of  
504 medical treatment, and facility were used as allocation factors.

505

### 506 7.4. Random allocation by minimization method

507 Each allocation factor will be summed, and if the difference between the two groups is  
508 greater than 2, the patient will be assigned to the allocation group with fewer allocation  
509 factors. If the difference between the two groups is less than 2, random assignment will  
510 be done to the randomly assigned group. The allocation factors will be entered into the  
511 UMIN INDICE cloud system in front of the therapist/participant or via online screen  
512 sharing during Week 1, and the allocation will be done on the spot.

513

## 514 8. Masking

515 Due to the nature of the intervention, this study cannot be masked to the  
516 therapist/participant. Statistical analysts will not be able to review the results until the  
517 end of the study. In addition, REDCap keeps a complete history, so the history can be  
518 traced for any evidence of confirmation of the results.

519 Masking: Statistical Analysts  
520 Not Masking: Participants, Therapists, Outcome adjudicators  
521

522 9. Discontinuation criteria

523 There will be two types of discontinuations from the study: intervention discontinuation  
524 and evaluation discontinuation.  
525

526 9.1. Deviation from protocol treatment

527 Any of the following will be considered a deviation from the protocol treatment. In such  
528 a case, the participant has not dropped out of the study, and periodic evaluation will be  
529 conducted unless the participant withdraws consent for evaluation.

530 (1) If the participant has never received any intervention treatment  
531 (2) When the intervention interval is more than 3 weeks.  
532 (3) When the participant has received additional treatment for OAB at another hospital.  
533 (4) When there are no valid data after the start of treatment.  
534

535 9.2. Discontinuation of intervention

536 If any of the following conditions apply, the protocol treatment will be discontinued at  
537 the discretion of the physician in charge of the study. In such cases, the participant is not  
538 dropped from the study, and subsequent periodic evaluations will be conducted unless  
539 the participant withdraws consent for the evaluation.

540 (1) When the participant wishes to discontinue the intervention  
541 (2) When a serious AE occurs and it is deemed difficult to continue the intervention  
542 (3) When the physician in charge of the study determines that the harm of continuing  
543 the intervention outweighs the benefit for some reason, although no serious AE has  
544 occurred  
545 (4) Other cases in which the investigator deems it inappropriate to continue the  
546 intervention.  
547

548 9.3. Discontinuation of valuation

549 If a study participant withdraws consent for a periodic evaluation, no further follow-up  
550 will be conducted.

551

552 10. Reporting of adverse events and ensuring the safety of study participants

553 10.1 Definition of adverse events

554 Adverse events (AEs) are any unwanted or unintended signs or symptoms that occur in

555 study participants, regardless of whether or not they are causally related to the

556 intervention. For each AE, the severity, severity, transposition, and causal relationship to

557 the intervention will be ascertained.

558

559 10.2 Measures to be taken and reporting procedures in case of AEs according to the

560 Pharmaceutical Affairs Law

561 Since all oral treatments in this study are within the approved dosage and administration,

562 the physician in charge will report to the MHLW if necessary, in accordance with

563 "Article 77-4-2, Paragraph 2 of the Pharmaceutical Affairs Law" and "Kyoto University

564 Graduate School of Medicine and Faculty of Medicine and Kyoto University Hospital

565 Medical Ethics Committee Operating Procedures".

566

567 10.3. Measures to be taken and procedures for reporting AEs according to the Ethical

568 Guidelines for Clinical Research

569 In the event of a serious AE, the physician in charge will take necessary and appropriate

570 measures to ensure the safety of the participant. According to the Ethical Guidelines for

571 Clinical Research Q&A, what is a serious AE?

572 A) Deadly

573 B) Life-threatening

574 C) Requiring hospitalization or prolonged hospitalization for treatment

575 D) Results in permanent or significant disability or dysfunction

576 E) Inherited birth defects.

577 The term "serious AE" refers to the following. If a serious AE is suspected, within 48

578 hours, the physician in charge will evaluate whether or not the event constitutes a

579 serious AE, regardless of whether or not it is causally related to the drug, in accordance

580 with the AE Reporting Protocol. If it is determined to be a serious AE, the PI will report

581 it to the Ethics Committee of the respective institution within 72 hours. The PI will also

582 notify all investigators, who will take necessary action based on the information

583 provided by the PI.

584

585 10.4 Anticipated adverse events

586 AEs associated with CBT will not occur in the pilot study and are not anticipated. When

587 taken concomitantly, anticholinergics or  $\beta$ 3-adrenoceptor agonists are used. AEs  
 588 associated with oral treatment include the following:

589 Anticholinergics

590 Main side effects: dry mouth and dry mouth, constipation, photophobia, blurred vision,  
 591 dysuria, drowsiness, stomach discomfort

592 Serious side effects: glaucoma, urinary retention, hepatic dysfunction, paralytic ileus,  
 593 hallucinations/delirium, QT prolongation, ventricular tachycardia

594

595 Beta 3-adrenergic receptor agonist

596 Main side effects: constipation, dry mouth

597 Serious side effects: urinary retention, hypertension

598

599 11. Statistical consideration

600 11.1 Sample size and rationale

601 Assuming a significance level of 5% bilaterally, a power of 80%, a symptom score  
 602 difference between groups (OAB-q) of 10, and a standard deviation of 20, the sample  
 603 size is 128 patients in both groups. Assuming a dropout rate of 15%, the target number  
 604 of participants is 150 in both groups.

605

606 11.2. Analysis participants

607 As an intention-to-treat (ITT) analysis, all participants for whom allocation have been  
 608 initiated will be included in the analysis. Only patients who adhere to this protocol (Per  
 609 Protocol Set: PPS) will also be analyzed as a sensitivity analysis.

610 Definition of PPS: Participants who meet the following 4 criteria

611 (1) Patients have received all intervention treatments.

612 (2) Intervention interval is less than 3 weeks.

613 (3) Patients have not received additional medical treatment for OAB at other hospitals

614 (4) All measurement data are available.

615

616 11.3 Statistical analysis

617 11.3.1 Primary analysis

618 A mixed-effects model with repeated-measures (MMRM) will be used to analyze the  
 619 primary outcome, the HRQoL total score of OAB-q, under the assumption of missing at  
 620 random. Estimates of the least squares mean group difference, 95% confidence interval,  
 621 and p-value will be calculated as the result of group  $\times$  time point estimation with the  
 622 change from baseline to each measurement point as the objective variable, treatment

group, time point, OAB severity, interaction between treatment group and time point as fixed effects, study participants as variable effects, and baseline values as covariates. Week 13 is the assessment point for the primary analysis. A multiple-testing procedure will be used to control for the familywise type I error rate at a two-sided significance level of 0.05. If the primary analysis at week 13 shows statistical significance, testing of other assessment points of the primary outcome is to be performed in a hierarchical manner: week 9 and week 5.

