##### 274 (3) Lifestyle modifications

275 Identify lifestyle habits that may be risk factors for OAB (excessive water intake,  
 276 caffeine consumption, alcohol consumption) and establish strategies to improve them.

277 (4) Pelvic floor muscle training

278 Weak pelvic floor muscles are considered one of the causes of OAB. In conjunction  
 279 with proper posture and breathing techniques, increase pelvic floor muscle strength  
 280 through repeated awareness and contraction/relaxation exercises.

281 (5) Exposure

282 While the urge to urinate can be avoided by emptying the bladder frequently, the act of  
 283 frequent urination actually promotes the urge to urinate, leading to a vicious cycle.

284 Exposure (endurance) to the uncomfortable situation (urge to urinate) is encouraged to  
 285 increase tolerance to the urge (to extend the interval between urinations). A step-by-step  
 286 schedule should be planned, and the urination interval should be gradually increased by  
 287 consistently following the schedule.

288 (6) Relapse prevention

289 Review the series of sessions and compare the condition before and after treatment. List  
 290 the positive and negative aspects and help the participants solve problems independently,  
 291 such as how to continue the treatment in the future or what to do in case of symptom  
 292 exacerbation.

293       Using these six techniques, interventions that may be effective for OAB are  
 294 selected, and the therapist and the research participant collaborate to set treatment goals  
 295 and assign homework for each session. Each session consists of 30 minutes and  
 296 includes (1) introduction, (2) agenda, and (3) summary. The overall treatment will  
 297 comprise of (1) an introduction phase (1 session), (2) a practice phase (2 sessions), and  
 298 (3) a relapse prevention phase (1 session), totaling 4 sessions. As a basic rule,  
 299 interventions will be conducted every week, but a maximum interval of three weeks will  
 300 be allowed (an interval of more than three weeks will be considered a deviation from  
 301 the intervention). If the patient is already on oral therapy, the CBT should be  
 302 coordinated with the oral therapy.

303 Due to concerns about the risk of novel coronavirus transmission, the intervention will  
 304 be conducted online using a web conferencing application for those who wish to  

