| 4        | Review session 3 and homework
Relapse prevention
Plan the future's goal and encourage to continue the techniques
Total review                                                                                                                                                                             |

313

314

315 5.2. Therapist

316 The treatment therapist in this study shall be qualified as a specialists and supervisors  
 317 certified by the Japanese Urological Association, with a minimum of 10 years of clinical  
 318 experience. Additionally, participation in the CBT workshop, a training program  
 319 conducted by the Ministry of Health, Labor, and Welfare, is mandatory.

320

321 5.3 Assurance of Quality of Intervention

322 To ensure the quality of interventions, a review committee comprising urologists,  
 323 obstetricians/gynecologists, psychiatrists, clinical psychologists, and physical therapists  
 324 was established, and a treatment manual was developed. The therapist will conduct  
 325 interventions in accordance with this manual. A checklist is prepared for each session to  
 326 verify the achievement of each item.

327

328 5.4. Treatment of the control group  
329 CBT will not be administered during the study period. If the patient is receiving a drug  
330 treatment, only the baseline treatment will be continued. CBT will be provided after the  
331 completion of the study. Online CBT using a web conferencing application will be  
332 conducted for those who wish to participate.  
333

334 6. Data collection  
335 6.1 Baseline characteristics  
336 Age, height, weight, medical history, childbearing experience, menopause, highest  
337 education level completed, marital status, occupational history, and history of dysuria  
338 treatment will be assessed using a questionnaire at baseline.  
339

340 6.2. Outcomes  
341 Primary outcome:  
342 - Overactive Bladder Questionnaire (OAB-q) HRQoL total score (2)  
343 This is a QOL self-reported questionnaire specific to OAB. It consists of questions  
344 regarding the degree of distress and QOL due to symptoms. Week 13 (end of follow-up)  
345 is the primary assessment point. The HRQoL total score of the OAB-q is calculated on a  
346 100-point scale as follows: Minimum Clinical Important Difference (MCID) is 10  
347 points (20).  
348  $[150 - (\text{Question Score } 9+10+11+12+13+14+15+16+17+18+19+20+$   

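### The per-protocol set in section 11.2 is wrong as written: no control can enter it, its interval limit conflicts with 5.1 and 9.1, and it requires complete data on every instrument

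*Protocol*

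**What the plan says.** Section 11.2 makes intention-to-treat the main analysis and adds the PPS. The set is introduced by "Definition of PPS: Participants who meet the following 4 criteria". No arm is named, either there or in the criteria. Those at issue are:

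- "1) Patients have received all intervention treatments"
- "2) Intervention interval is less than 3 weeks"
- criterion (3), which bars additional OAB treatment obtained at other hospitals
- "4) All measurement data are available"

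Section 11.3.4 uses this set for a sensitivity analysis, next to multiple imputation under missing at random.

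Other sections bear on the criteria. For the control group, 5.4 says "CBT will not be administered during the study period", and 7.2 has controls told that they will be offered CBT only once the study is complete. On spacing, 5.1 says "interventions will be conducted every week, but a maximum interval of three weeks will" be allowed, and 9.1 lists as a deviation "2) When the intervention interval is more than 3 weeks". Section 9.1 also lists "1) If the participant has never received any intervention treatment".

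**The concern.** A per-protocol set should contain the participants in each arm who did what the protocol asked of that arm. This definition does not do that. A control managed exactly as planned fails the first criterion, and a CBT participant whose spacing was within the permitted limit can fail the second. A participant in either arm with full data on the primary outcome can fail the fourth.

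At stake is one of the two sensitivity analyses in 11.3.4. The other, multiple imputation, rests on the same missing-at-random assumption as the primary mixed model, so the PPS is the only listed check of a different kind. If the wording stays, someone must decide at analysis which criteria to waive and for whom. Unless that is settled beforehand, the decision may come after the data are visible.

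**Working it through.** **1. The protocol's own sample size (11.1).** Inputs: two-sided 5%, power 80%, difference 10, SD 20, 1:1 allocation. Standardised difference = 10/20 = 0.5. The normal approximation gives 2 × (1.960 + 0.842)² / 0.5² = 62.8, so 63 per arm. The t-based solution is 63.77, so 64 per arm and 128 in total, as stated. Allowing for 15% dropout, 128/0.85 = 150.6, against the stated 150. The sample size is not in question. It gives about 150/2 = 75 per arm.

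**2. Who can meet criteria (1) and (2).**

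| | CBT arm | Control arm |
|---|---|---|
| CBT sessions during the study | 4 planned (5.1) | 0 (5.4, 7.2) |
| Criterion (1), all sessions received | can be met | cannot be met |
| Criterion (2), session interval | defined | no sessions, so no interval exists |
| 9.1(1), never treated counts as a deviation | only if no session is attended | true of every control managed as planned |

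All four criteria must hold, so the literal set contains at most 75 CBT participants and 0 of about 75 controls. No between-group estimate exists.

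**3. The interval rule.**

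| Longest interval | 5.1 | 9.1(2) | PPS criterion (2) |
|---|---|---|---|
| under 3 weeks | allowed | no deviation | included |
| exactly 3 weeks | allowed | no deviation | excluded |
| over 3 weeks | deviation | deviation | excluded |

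The conflict is confined to the middle row. The documents do not say how many participants would fall there.

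**4. The complete-data rule.** Section 6.3 lists seven patient-completed instruments (OAB-q, OABSS, KHQ, global impression, EQ-5D-5L, HADS and the voiding chart), besides treatment compliance, at four time points: 7 × 4 = 28 records per person. Criterion (4) is not restricted to the primary outcome, so one missing week-9 voiding chart removes a participant whose OAB-q is complete at all four. The KHQ scoring in 6.2 also sets the personal-relationships domain to missing when its two items sum to zero. On a strict reading, a fully completed form could therefore fail. By contrast, 9.1(4) counts as a deviation only the absence of any valid data after treatment starts. The mixed model in 11.3.1 uses partially observed participants under missing at random.

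**5. Added treatment.** Criterion (3) covers other hospitals only and matches 9.1(3). Section 5.4 says that controls on drugs continue baseline treatment alone. OAB treatment added at a trial hospital departs from 5.4 but is not caught by criterion (3).

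**6. What different readings leave.** The losses below are assumptions. Power is for a two-sample t-test with difference 10 and SD 20.

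| Reading | Further CBT loss for non-adherence | CBT | Control | Power |
|---|---|---|---|---|
| Literal | – | at most 75 | 0 | none |
| (1)–(2) for CBT only, (4) kept, 15% incomplete per arm | 0% / 10% / 20% | 63.8 / 57.4 / 51.0 | 63.8 | 80% / 78% / 75% |
| Same, 25% incomplete per arm | 0% / 10% / 20% | 56.2 / 50.6 / 45.0 | 56.2 | 74.8% / 72.5% / 69.7% |
| (1)–(2) for CBT only, (4) dropped | 0% / 10% / 20% | 75 / 67.5 / 60 | 75 | 86% / 84% / 82% |

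The last row is an upper bound, because participants kept with partial data contribute less than full information.

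**The case against.** The strongest reply is that the intent is plain. The sentence before the criteria restricts the PPS to people who kept to the protocol, and for a control that means having no CBT. Criteria (1) and (2) would then concern the CBT arm only, and 9.1(1) likewise, since it deals with a treatment that controls are not assigned. Membership by arm is often spelled out in a statistical analysis plan, which is not at hand. This reading is probably what was meant, and an analyst would be unlikely to run a one-arm analysis. But the protocol does not leave the matter open: it states a four-part rule, and that rule gives an empty control group. A later plan would have to contradict it, not merely fill it in.

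Several further replies stand and limit the point:

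- The interval mismatch is a boundary case in a programme scheduled weekly.
- Criterion (3) agrees with 9.1(3), so the tension is only with 5.4. Excluding everyone with any medication change would not be a clean remedy, because medication change is itself a secondary outcome.
- Requiring complete data can be a deliberate choice for a per-protocol set. The difficulty is its reach over every instrument and visit, out of line with 9.1(4).

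**Conclusion.** The PPS definition is wrong as written and should be corrected. Severity is minor to moderate. The exclusion of controls and the conflict at exactly 3 weeks follow from the text alone; the set sizes and power figures rest on the assumed losses shown.

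Four stronger conclusions might be inferred, and the documents do not support them:

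- **That the trial's main result is compromised.** The primary estimate, its test, the sample size and the hierarchical testing in 11.3.1 do not use the PPS.
- **That many CBT participants would be lost through the interval rule.** Only gaps of exactly 3 weeks are affected, and no count is given.
- **That the bias from comparing completers with controls can be sized from the 15% dropout rate.** Sections 9.2 and 9.3 separate stopping the intervention, after which evaluation continues, from stopping evaluation. The protocol gives neither a session-completion rate nor an outcome gap between completers and others. The direction, favouring CBT, is plausible if non-completers do worse, but that too is an assumption.
- **That restricting the criteria by arm removes this selection or makes the result less favourable to CBT.** It makes the analysis computable. The contrast remains between adherent CBT participants and controls not selected on adherence.

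**What to change.** 1. In 11.2, state that criterion (1) and the interval criterion apply to the CBT arm only, and define adherence in the control arm as no CBT before the week-13 assessment. Make the same arm restriction in 9.1(1).
2. Reconcile the interval threshold across 5.1, 9.1 and 11.2 so that one rule decides both deviation and PPS membership. Which threshold to adopt is for the investigators.
3. Drop criterion (4), or limit it to the OAB-q HRQoL score. The limited form still conditions on data observed after randomisation, and the text should say so.
4. Reconcile criterion (3) with 5.4 on OAB treatment added at a trial hospital, bearing in mind that medication change is a listed outcome.
5. In 11.3.4, call the PPS analysis supplementary and state that it compares adherent CBT participants with controls not selected on adherence, so it may favour CBT.

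The cost is a wording amendment to 9.1, 11.2 and 11.3.4, and to 5.1 if its threshold is the one changed. No new data are needed, and the sample size and primary analysis stay as they are. The amendment should be made before outcome data are seen.

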199 intervention. Based on the results of the pilot study, we concluded that it was

200 worthwhile to evaluate the efficacy of CBT for OAB and decided to design this study.

201

202 2. Purpose

203 The purpose of this study is to establish CBT for OAB based on conventional  
 204 behavioral therapies and to evaluate its efficacy in women with moderate to severe  
 205 OAB in a randomized controlled trial.  
 206

207 3. Study design  
 208 Open-label, parallel-group, multicenter, 1:1 randomized controlled trial  
 209

210 4. Selection of participants  
 211 4.1. Institutions  
 212 Department of Urology, Kyoto University Hospital  
 213 Department of Urology, Kyoto City Hospital  
 214 Department of Urology, Asukai Hospital, Kyoto Civil Medical Federation Ichioka  
 215 Urology Clinic  
 216

217 4.2 Inclusion and exclusion criteria  
 218 Inclusion criteria:  
 219 (1) Women between 20-80-year-old;  
 220 (2) Participants not having undergone any OAB treatment for more than 6 weeks or  
 221 participants taking pharmacotherapy lasting more than 6 weeks for OAB;  
 222 (3) Participants diagnosed with OAB based on their OAB symptom score (OABSS)\* (a  
 223 total OABSS score  $\geq 3$ , with an urgency score  $\geq 2$ ), with the total score being higher than  
 224 6 (OABSS; 6 to 11 points indicate moderate severity, 12 to 15 points indicate moderate  
 225 severity) (1);  
 226 (4) An Eastern Cooperative Oncology Group (ECOG) Performance Status of Grade 0;  
 227 and  
 228 (5) Participants who are able to understand explanations and sign a written informed  
 229 consent.  
 230

231 \*Overactive Bladder Symptom Score (OABSS):  
 232 It is a symptom score for OAB developed in Japan and used worldwide for diagnosis  
 233 and severity assessment (1). A urinary urgency score (Question 3) of 2 or higher and a  
 234 total score of 3 or higher are considered a diagnosis of OAB. Regarding severity, a total  
 235 score of 5 or less is considered mild, a score of 6-11 moderate, and a score of 12 or  
 236 more severe.  
 237

238 Exclusion criteria

- 239 (1) Abnormalities around the bladder (e.g., bladder cancer, bladder calculus, interstitial  
240 cystitis, endometriosis);  
241 (2) Urinary tract infection;  
242 (3) Surgery for urinary incontinence;  
243 (4) Pregnancy;  
244 (5) Disability to understand Japanese;  
245 (6) Depression;  
246 (7) Dementia; and  
247 (8) Participants judged otherwise unsuitable for participation by the researchers.  
248

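### The primary MMRM adjusts for one of the five minimisation factors; adding the other four costs almost nothing and may gain a little precision

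*Protocol*

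**What the plan says.** Section 7.3 of the protocol numbers five minimisation factors: age (2 levels), OAB severity (2), oral treatment (3), institution (4) and, last, "5) Intervention method: 2 levels: face-to-face, web conference". Its closing rationale is shorter than its list. It ends with "medical treatment, and facility were used as allocation factors" and does not mention intervention method.

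Section 11.3.1 writes out the primary model. The outcome is change from baseline in the OAB-q HRQoL total score. The terms are "group, time point, OAB severity, interaction between treatment group and time point as fixed effects", with participant as a random effect and the baseline score as a covariate. Week 13 is the primary time point.

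Section 11.3.2 applies the same methods to the secondary outcomes. The sensitivity analyses in 11.3.4 (per-protocol set, multiple imputation) do not bring in the missing factors. No section explains why severity is kept and the other four are dropped.

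**The concern.** Minimisation makes the arms alike on the chosen factors. If such a factor predicts outcome, the difference between arm means varies less from one realisation of the trial to another than it would under simple randomisation. A model without the factor does not see this. It counts the variation between factor levels as residual noise and reports a standard error for an allocation less balanced than the one used.

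At stake are the width of the primary confidence interval and some power. The protocol lists the model terms and includes one allocation factor among them, so the omission is a stated choice and not a detail left to a statistical analysis plan. All four missing factors must be known for every participant at allocation, so including them requires no new data.

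**Working it through.** **The plan's own figure.** Section 11.1 gives: "Assuming a significance level of 5% bilaterally, a power of 80%, a symptom score" "difference between groups (OAB-q) of 10, and a standard deviation of 20, the sample" "size is 128 patients in both groups. Assuming a dropout rate of 15%, the target number" "of participants is 150 in both groups". Section 3 gives 1:1 allocation.

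- Normal approximation: n per arm = 2 × (1.960 + 0.842)² × (20/10)² = 62.8, so 63 per arm, 126 in total.
- Two-sample t-test: 64 per arm, 128 in total, power 80.1%. This is the stated figure.
- Dropout: 128/0.85 = 150.6, against the stated 150.

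The size reproduces and uses no covariates. The 80% target therefore does not depend on adjusting for any factor.

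**Effect of the omission.** Let R² be the share of residual variance, after baseline score and severity, that the four omitted factors explain. The documents do not give R². I assume 0% to 15%. Let s = √(1 − R²). If allocation balances the factors, the true standard error is s times the one the shorter model reports. At nominal 80% power the expected z is 1.960 + 0.842 = 2.802.

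- Excess of the reported standard error: 1/s − 1
- True two-sided type I error: 2 × [1 − Φ(1.960/s)]
- Power without the factors: Φ(0.842/s)
- Power with the factors: Φ(2.802/s − 1.960)
- Sample size multiplier for the shorter model to match the fuller one: [1 + (1.960/2.802)(1 − s)]²

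| R² | s | SE too large by | Type I error | Power without | Power with | Gain (points) | Extra participants on 150 |
|---|---|---|---|---|---|---|---|
| 0 | 1.000 | 0% | 5.0% | 80.0% | 80.0% | 0 | 0 |
| 0.05 | 0.975 | 2.6% | 4.4% | 80.6% | 82.0% | 1.4 | 5 |
| 0.10 | 0.949 | 5.4% | 3.9% | 81.2% | 84.0% | 2.7 | 11 |
| 0.15 | 0.922 | 8.5% | 3.4% | 81.9% | 86.0% | 4.0 | 17 |

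Gains are taken before rounding. The power without the factors also rises above 80%, because balance shrinks the true variability whether or not the model knows of it.

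**Check by simulation.** Minimisation on five factors was simulated with 128 participants, one time point, assumed factor frequencies and 4,000 runs per setting. A summed difference of 2 or more triggered assignment to the smaller arm; section 7.4 does not say what happens at exactly 2.

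- R² = 0: power 80.2% with either model, so the extra terms cost essentially nothing.
- R² = 0.05: power 81.2% with severity only, 82.5% with all five factors.
- R² = 0.10: mean reported standard error 3.53 against a true 3.44; type I error 4.2%; power 81.6% against 83.9%.
- R² = 0.20 (beyond the range above): 3.53 against 3.16; type I error 3.1%; power 82.9% against 88.2%.

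Minimisation balances imperfectly, and the simulation has its own random error. At R² = 0.10 the excess in the standard error is 3.53/3.44 − 1 = 2.6%, smaller than the formula's 5.4%. The direction agrees, and the gains in power are close to the formula's.

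**Degrees of freedom.** Age 1, oral treatment 2, institution 3, intervention method 1: 7 in total.

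**The case against.** The best defence is that nothing here is invalid. The estimate is unbiased, the test errs on the cautious side, the intervals over-cover, and a positive result would be safe. All of that stands.

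The size is also uncertain. Baseline OAB-q is already in the model and may absorb much of what age, drug treatment and site would explain, so R² could be near zero. That stands too, and it is why the range starts at 0%.

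Three stronger readings are tempting, and the protocol does not support them:

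- A reader might infer that the trial falls short of its planned power. It does not: section 11.1 sizes it for an unadjusted comparison with an SD of 20. The loss is only relative to a better model.
- A reader might set the adjusted 82% to 86% against a nominal 80% and claim 2 to 6 points. That applies the balance to type I error but not to power. The proper comparators are 80.6% to 81.9%.
- A reader might infer that section 7.3 declares all five factors prognostic. For age, severity and medication it argues mainly that the effect of the intervention may differ, which is effect modification; subgroup analyses in 11.3.3 address that. It does call age a leading risk factor for OAB, and it expects patient backgrounds to differ between facilities. For intervention method it gives no rationale. The standard error argument needs main effects on outcome, and the protocol makes that case only in part.

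None of this is a reason for keeping one allocation factor and dropping four.

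**Conclusion.** The point holds as a free improvement with a minor efficiency gain. It is certain that the primary model contains one of five minimisation factors and that no reason is given. The direction is also clear: to the extent that the omitted factors predict outcome, the analysis is conservative. The size rests on an assumed R². It runs from nil at 0% to about 4.0 points of power at 15%, where matching the fuller model would take about 17 more participants on top of 150. The formulae also assume near-complete balance on the factors and a single comparison at Week 13. No conclusion that the shorter model would reach becomes unsafe because of this.

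**What to change.** In section 11.3.1, before analysts see any results, add age group (20–64, 65–80), oral treatment (3 levels), institution (4 levels) and intended intervention method as fixed effects beside OAB severity and baseline OAB-q. Use the values recorded at allocation. State in advance how institutions that recruit few participants will be pooled. Use the same covariates in the models for the continuous secondary outcomes; section 6.2 makes PGI-I, PGI-S and satisfaction binary, so those need their own statement. If the shorter model is preferred, give the reason.

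The cost is a sentence or two and about 7 degrees of freedom among roughly 128 evaluable participants, with no new data. Making the change after results are known would be open to challenge.
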